# A randomized controlled trial to examine the impacts of disclosing personalized depression risk information on the outcomes of individuals who are at high risk of developing major depression: a research protocol

**DOI:** 10.1186/s12888-019-2270-9

**Published:** 2019-09-18

**Keywords:** Major depression, Multivariable risk predictive algorithms, High risk, Early identification, General population, Self-help, Psychological distress

## Abstract

**Background:**

Major depressive disorder is one of the most prevalent and disabling forms of mental illness in the general population. One public health strategy that may reduce the disease burden is early identification and prevention - identifying people who are at high risk and intervening to prevent symptoms from progressing into a major depressive episode (MDE). Multivariable risk predictive algorithms (MVRP) have been developed to estimate personalized risk (probability) of an MDE. The purpose of this trial is to answer the questions: (1) Does disclosure of personalized depression risk information promote high-risk individuals to take preventive actions? (2) Will disclosure of personalized depression risk information negatively affect the mental health of those at high risk?

**Methods:**

We are recruiting 350 high-risk men and 350 high-risk women across the country. Individuals are eligible, if they: (1) are 18 years or older, (2) have not had a depressive episode in the past two months, (3) are at high risk of MDE based on the MVRPs (predicted risk of 6.5% + for men and of 11.2% + for women), (4) can communicate in either English or French, and (5) agree to be contacted for follow-up interviews. The MVRPs were developed and validated using longitudinal data from over 10,000 Canadians across the country. Eligible participants are randomized into (1) the control group, and (2) the group receiving personalized depression risk information. The participants are assessed at baseline, 6 and 12 months regarding accuracy of risk perception, use of self-help strategies and changes in psychological distress and functioning. Qualitative interviews are conducted in sub-samples of the intervention groups to explore how the personalized information affects risk perception, self-help behaviors and mental health.

**Discussion:**

MVRPs can be used for risk stratification and planning preventive actions. The personalized risk information produced by MVRPs may also empower users to actively engage in self-management. This trial will contribute to the knowledge base about the potential health benefits and psychological harms associated with the provision of personalized depression risk information that will inform future implementation and patient-physician communication in the clinical settings.

**Trial registration:**

NCT02943876. Date of trial registration: October 21st, 2016.

## Background

There is a pressing need for prevention of major depressive disorder (MDD). The Global Burden of Disease study [1] reported that MDD was the #2 leading cause of disease burden worldwide in 2010. Despite a significant increase in mental health service use in the past two decades, there has been no a measurable change in the prevalence of MDD in various countries [2]. The unchanged disease burden associated with MDD suggests that more effective efforts in early identification and prevention are needed, e.g., identifying people who are at high risk and taking preventive actions to lower the risk.

In medicine, multivariable risk prediction (MVRP) models are often used to estimate an individual’s absolute risk (probability) of developing a disease in a given time period, based on the individual’s current exposure to a key set of known risk factors (i.e., baseline risk). Well-known examples include the Framingham risk prediction algorithms for cardiovascular disease [3]. The Framingham risk algorithms are used by clinicians in predicting the risk of developing coronary disease in individuals free of the disease. The Framingham risk functions underpin several of the current policies for preventive interventions, including statin therapy for those with relatively high risk of cardiovascular disease.

There is a paucity of research in risk prediction for mental disorders. This is partly due to the lack of population-based longitudinal studies on mental disorders with frequent assessments. In 2013, our team developed and validated sex-specific MVRPs for MDE in the Canadian general population [4]. The MVRPs were developed to predict 4-year risk of MDE, using longitudinal data from 4737 men and 5864 women who were randomly selected across Canada, and who had not had a MDE in the past year prior to the baseline. The MVRPs includes questions about personal and family history of MDD, ongoing negative life stressors and childhood traumatic experience. Predictors in the MVRPs are in Table 1. The MVRPs had good discriminative power (men: C = 0.7953; women: C = 0.7667), and excellent calibration with the data. In men, the observed and predicted 4-year risk of a MDE was 5.15% and 5.25%, respectively; in women, the observed and predicted 4-year risk of a MDE was 8.27 and 8.31% [4]. We validated the MVRPs in Canadians followed during a different time period [4].

**Table 1 Tab1:** The predictors in the sex-specific multivariable risk predictive algorithms for major depression

	Prediction Algorithm for Women	Prediction Algorithm for Men
Predictors that do not change with time	1. Age (continuous)	1. Age (continuous)
	2. Past major depressive episode (MDE)	2. Past major depressive episode
	3. Family history of MDE	3. Family history of MDE
		4. Physician diagnosed diabetes
	Childhood Trauma	Childhood Trauma
	4. Being traumatized for years	5. Being sent away from home
	5. Being sent away from home	6. Parents divorced
		7. Parents abused alcohol/drugs
Predictors that change with time	6. Annual personal income	8. Self-rated chronic stress
	7. Self-rated health	9. Others expect you too much
	8. Activity restrictions	10. Lack of money
	9. Satisfaction with oneself	11. Feeling everything is an effort
	10. Self-rated chronic stress	12. Took anti-depressants last month^a^
	11. Others expect you too much	13. Took sleeping pills last month^a^
	12. Family member in bad health	14. Being physically attacked in the past year
	13. Daily smoking	15. Partner had unwanted pregnancy in the past year
	14. Changed job for a worse one in the past year	
	15. Major financial crisis in the past year	
	16. Having depressed mood/lost of interest for 2 weeks in the past year	
	17. Talked to health professionals for mental health issues in the past year. ^a^	

^a^Service and medication use indicate severity of stress, rather than increased risk

MVRP tools may not only enable health professionals to identify high risk people, but also serve as communication tools to inform consumers about their health status and to empower them to actively engage in self-management. One goal of personalized risk estimates is to promote involvement of consumers in health decisions [5]. Research in cardiology and oncology [5, 6] shows that disclosing personalized risk to consumers is an effective method to achieve consumer involvement in health decisions. Because risk prediction models for MDD are new and the literature on risk disclosure is absent in psychiatry, we have no knowledge about whether provision of this information improves risk perceptions and whether high risk people will act upon the information to engage in self-help. Second, since 2013, we have directly engaged over 500 policy makers, clinicians and the general public to disseminate the prediction tools. Stakeholders have consistently indicated that a question needs to be answered before implementation: *will the provision of personalized depression risk information lead to increased psychological distress in high risk people*? As risk prediction models are new in psychiatry, there are no studies that address these notable knowledge gaps. Clearly, we need to provide answers to these practice and policy pertinent questions before moving forward to implementation.

## Methods/design

Given the background, the aim of the proposed randomized controlled trial is to answer the following research questions: (1) Does disclosure of personalized depression risk information promote high-risk individuals to take preventive actions? The effect of risk prediction may be maximized if these individuals actively engage in early prevention. (2) Will disclosure of personalized depression risk information negatively affect high-risk people’s mental health status? To safely implement the prediction algorithms, we need to ensure that the disclosure will not lead to increased psychological distress.

This study is a mixed-methods randomized controlled trial (RCT) with an embedded qualitative component. The RCT has one intervention arm (receiving personalized depression risk information) and one control arm (1:1). The target population are individuals in the community who are at high risk of major depression. The personalized depression risk is generated using the sex-specific MVRPs for MDE that we developed in Canadians aged 18+ years old [4]. Thus, the inclusion criteria are:
no MDE at baseline, or if had a MDE in the past 12 months, the individuals were in full remission for at least 2 months before the interview (see below the question),aged 18+ years,at high risk of MDE based on the algorithms (predicted risk of 6.5% + for men and of 11.2% + for women) [4],agreement to be contacted for follow-up assessments, andno language barriers to English or French.

The status of remission was assessed by the question: “In the past 2 months or longer, has your mood been much improved or back to normal AND you DIDN’T have the symptoms of.....?” This question was adopted from the US National Epidemiological Survey on Alcohol and Related Conditions [7]. Because the prediction algorithms are sex-specific, we are recruiting 350 men and 350 women at baseline. After baseline assessment for eligibility, participants are randomized into intervention and control groups, in men and women separately.

Based on systematic reviews on risk communication [5, 6], the trials targeting behavioral and health status changes required 6 months to 12 months follow-up. Therefore we are following participants for 1 year with follow-up assessments at 6 and 12 months. The RCT adheres to CONSORT and SPIRIT guidelines [8]. An operational flow chart is in Fig. 1. The baseline and follow-up data collection was carried out using Computer Assisted Telephone Interview which automatically saves the data once the interview is completed. To obtain in-depth information about how the personalized depression risk information is processed by participants and how the information affects them emotionally, we conduct qualitative interviews 1 month after the personalized risk information is disclosed. To understand how the personalized risk information affects participants’ health behaviors, we conduct another round of qualitative interviews at 12 months. All collected data will be kept in a pass-word protected computer in the principle investigator’s office which is under 24/7 security surveillance. Only the project coordinator who is not involved in randomization and data collection has access to the data with personal identification information. Data without personal identification information will be analysed. Only aggregate results will be presented and published. This study has been approved by the Ethics Review Board of the Royal Hospital, Ottawa, Canada, and is reviewed by ERB on an annual basis.

**Fig. 1 Fig1:**
[figure not shown]
Project operational flowchart

### Recruitment

The target population for future preventive studies is high risk people in the general population. For the proposed study, we are recruiting eligible participants using the random digit dialing method (RDD). We have used the RDD for recruitment in other longitudinal studies [9, 10] and an ongoing national RCT [11]. Recruitment, screening, baseline assessment and randomization are completed by a telephone survey firm that has access to household telephone and validated cell phone numbers across the country. The recruitment and randomization procedures and questionnaire were pilot tested in 20 eligible participants, using a cognitive interviewing method [12].

A random sample of landline and cell phone numbers are selected. When a household is reached, the person who is 18+ years is assessed for eligibility. If a household has 2+ persons aged 18+ years, one is randomly selected. The interviewers explain the study objectives and procedures and answer questions. Potential participants are ensured confidentiality, that participation is voluntary and that they may withdraw at any time. Oral consent is obtained before assessment of eligibility by asking the question: “Do I have your consent to begin the survey?” The answer of “yes” and continued participation is deemed to be informed consent. The Research Ethics Board formally approved this consent.

Outcome measures are assessed at baseline, 6 and 12-month.

#### Perception of depression risk is assessed by asking

“How likely are you to get depression in the next 4 years?“ [13, 14] The answer can range from 0 to 100, where 0 = certain not to happen and 100 = certain to happen [13, 14].

*Self-management strategy use scale (SSUS)* was developed and validated by Morgan and Jorm [15]. The.

SSUS assesses the frequency of using each of the 14 self-help strategies [15], including strategies supported by research evidence (e.g., physical exercise,20–23 mindfulness relaxation,24;25 and online cognitive behavior therapy [16, 17]). Frequency of use can be rated on a 5-category scale. The SSUS has good internal consistency (Cronbach’s a = 0.80) [15].

*The Non-Specific Psychological Distress (K10)* is a 10-item screening scale intended to yield a global measure of distress based on questions about anxiety and depressive symptoms that a person has experienced in the most recent 4 week period [18]. The scale strongly discriminated between community cases and non-cases of DSM-IV disorders, with areas under the Receiver Operating Characteristic curve of 0.87–0.88 for disorders having Global Assessment of Functioning (GAF) scores of 0–70 and 0.95–0.96 for disorders having GAF scores of 0–50.28 We will compare the changes in the K10 scores over time between the groups to assess whether disclosing the personal risk leads to more psychological distress.

*Functioning impairments* is assessed by the question asking how the symptoms in the K10 affect functioning at home, work and school. We will also ask participants their number of days off work due to health problems in the past month.

*Sex-specific MVRPs for MDE* are administered to identify individuals who are at high risk for MDE, determine eligibility and assess accuracy of *perception of depression risk* over time. The algorithms have good discrimination (C statistic of 0.76 for women and of 0.79 for men), which is consistent with the range of C statistics of risk algorithms (0.75–0.80) in cardiology [19].

*Other baseline measures* include the *Composite International Diagnostic Interview – Short Form for **Major Depression* (CIDI-SFMD) is administered to determine eligibility for participation. The CIDI-SFMD is a structured diagnostic interview for MDE in the past year and has been used in all cycles of the National Population Health Survey conducted by Statistics Canada, based on the DSM-IV criteria [20]. The CIDI-SFMD was developed and validated at the University of Michigan [21]. Additionally we collect data about *demographic* and *socioeconomic* characteristics and *mental health service use* (at baseline and follow-up) using standard questions from Statistics Canada surveys.

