#### Baseline assessment

In eligible participants, the interviewer administers the K10, SSUS, and asks questions about absenteeism and perceived risk of MDE. Baseline assessment takes 20 to 25 min.

*Randomization* is carried out in men and in women. The telephone survey firm uses a survey software tool built by Voxco. The tool contains a random number generator which randomly creates a digit when the telephone script reads the function. The firm confirmed that this is comparable to the traditional method of using sealed opaque envelopes.

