### Intervention and control

For the participants in the intervention group, the personalized risk is disclosed and the interviewer informs the participants that they will be contacted again at 6 months and 12 months. The interest in receiving such personalized depression information has been confirmed by our recent pilot study using the same sampling method. Our pilot data (*n* = 200) showed that 100% of high-risk individuals were interested in knowing their risks. Participants in the intervention group are also informed that some may be contacted in 1 month for a 30-min qualitative interview. A package including the following materials is mailed to intervention participants: (1) thank-you letter, (2) general information about MDE, (3) self-help strategies [15] and a summary of research evidence supporting the effectiveness of self-help strategies, and (4) $20 incentive as appreciation of their participation. For participants in the control group, the interviewer informs them that they will be contacted again at 6 and 12 months. Their personal risks will be provided at the 12-month interview. They receive the same package as those in the intervention group.

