### Statistical analysis

All analyses will be carried out in men and in women separately, and by group assignment. We will perform an intention-to-treat analysis based on randomization. Each outcome will be analyzed with a separate regression model that includes intervention assignment and demographics, history of MDE and predicted risk at baseline as covariates.

Mixed ANOVA with a random intercept will be used to examine the effect of disclosing personalized depression risk information on changes in the SSUS scores, K10 scores and number of days off work. The mixed model will enable the repeated measures to be included in a single analysis and so that data from subjects not followed for the full year can be included. We expect no significant differences between the groups in changes of K10 scores and absenteeism at 6 and 12-month, i.e., disclosing the risk information does not lead to psychological and functioning harms. To examine the effect of risk disclosure on accuracy of perceived risk, we will first subtract participants’ perceived risk from the predicted risk. Positive values of the difference indicate underestimation of risk; negative scores indicate overestimation. We will recode difference scores into a dichotomous variable (≤10% vs > 10%) [13, 14], indicating whether perceived risk is “close” to the predicted risk. The proportions of accurate risk perception at baseline 6- and 12-month will be estimated and compared. Stratified analyses by demographic variables, history of MDE, baseline predicted risk levels will be conducted. Additionally, we will conduct the same analyses in participants who do not have missing outcome data (the completers).

Interim analysis will be conducted after 6-month follow-up. If the intervention group has a significantly higher incident proportion of major depression, and/or of suicidal behaviors, controlling for baseline covariates, than the control group, a team meeting involving staff of ethics review board will be held to review the results and determine whether the trial will be terminated.

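### The planned no-harm statement is wider than the design supports: no randomised comparison of distress or absenteeism covers roughly the first 22 weeks after disclosure

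*Protocol article*

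**What the plan says.** All of this is in the Protocol article.

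- **Order of events.** Under Baseline assessment: "In eligible participants, the interviewer administers the K10, SSUS, and asks questions about absenteeism and perceived risk of MDE". Under Methods/design: "After baseline assessment for eligibility, participants are randomized into intervention and control groups, in men and women separately". The baseline K10 therefore precedes disclosure.
- **Disclosure.** Under Intervention and control, for the intervention arm, "the personalized risk is disclosed and the interviewer informs the participants that they will be contacted again at 6 months and 12 months". No repeat disclosure is described.
- **Schedule.** Under Recruitment: "Outcome measures are assessed at baseline, 6 and 12-month".
- **Distress measure.** The outcome descriptions say that the K10 covers "anxiety and depressive symptoms that a person has experienced in the most recent 4 week period" and give it the deciding role for distress (quote cut before its last word): "We will compare the changes in the K10 scores over time between the groups to assess whether disclosing the personal risk leads to more psychological". The absenteeism item looks back one month.
- **Early contact.** Under Methods/design: "we conduct qualitative interviews 1 month after the personalized risk information is disclosed". Qualitative interviews puts the initial sample at 20 men and 20 women, all from the intervention arm.
- **Inference.** Statistical analysis expects no significant group difference in K10 change or absenteeism at 6 and 12 months, and glosses this as meaning that "disclosing the risk information does not lead to psychological and functioning harms".
- **Interim look.** The same section plans a comparison of incident major depression and suicidal behaviours between the arms after the 6-month follow-up.

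**The concern.** The second research question is whether disclosure harms mental health. Methods/design says that safe implementation requires assurance that distress does not rise, and sets no limit to lasting distress. The Background reports that stakeholders want this answered before the tool is used.

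Disclosure is a single dated event, and a reaction to it may be short. The two scales that carry the harm question look back about a month from interviews held half a year and a year later. The reason given for that schedule, in Methods/design, is the follow-up needed in trials of behavioural and health-status change. It does not mention how distress runs after someone is told of a high risk. If a reaction came and went in between, the K10 comparison would show little or nothing, and the planned wording would turn that into a statement that disclosure does no harm. The possible error lies in the direction of the result that the protocol expects.

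**Working it through.** The plan gives no figure of its own on this point. Its sample size calculation concerns the SSUS and does not bear on the gap.

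**Step 1: what the recall windows cover.** Inputs: disclosure at week 0; follow-up at 6 and 12 months, about weeks 26 and 52; recall of 4 weeks (K10) or one month (days off work).

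- The 6-month K10 covers about weeks 22 to 26, and the 12-month K10 about weeks 48 to 52.
- Initial period not covered: 26 − 4 = 22 weeks, or 22/26 = 85% of the first six months.
- Covered over the year: 2 × 4 = 8 of 52 weeks, or 15%.
- Days off work, with a one-month window, leave practically the same gap.

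**Step 2: what else could see the early period.**

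- 1-month interviews: initially 40 people in one arm, with thematic analysis and no distress score. They can describe a reaction but cannot compare arms.
- Interim analysis: a randomised comparison of incident depression and suicidal behaviours. It could register a severe early reaction, but distress below that level does not enter it.

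**Step 3: how much of a fading reaction would remain.** Everything about the reaction is assumed here, because the protocol gives neither its size nor its duration. With initial effect d0 and half-life h weeks, the effect at week t is d0 × 2^(−t/h). For d0 = 0.50 SD at week 24, the middle of the 6-month window:

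- h = 4: 0.50 × 2^(−6) = 0.008
- h = 6: 0.50 × 2^(−4) = 0.031
- h = 8: 0.50 × 2^(−3) = 0.063

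The mean over weeks 0 to 4 is d0 × (1 − 2^(−4/h)) / ((4/h) × ln 2), which gives 0.36, 0.40 and 0.42 SD for the same half-lives.

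**Step 4: chance of detection.** Completers per arm within each sex: 350 × 0.75 / 2 = 131, using the protocol's 75% response rate for 12 months. Power is taken as Φ(d × √(131/2) − 1.96), two-sided 5%, with d averaged over the recall window.

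| Initial d | Half-life (weeks) | Mean d, weeks 0–4 | Power if measured then | Mean d, 6-month window | Power at 6 months |
|---|---|---|---|---|---|
| 0.5 | 4 | 0.36 | 83% | 0.008 | 3% |
| 0.5 | 8 | 0.42 | 93% | 0.06 | 7% |
| 0.5 | 12 | 0.45 | 95% | 0.12 | 17% |
| 0.5 | 26 | 0.47 | 97% | 0.26 | 57% |
| 0.8 | 8 | 0.68 | above 99% | 0.10 | 12% |
| 0.8 | 26 | 0.76 | above 99% | 0.42 | 93% |

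The gap in Step 1 follows from the protocol's own schedule. Its consequence in Steps 3 and 4 depends on the assumed half-life: a short reaction leaves almost no trace at 6 months, while a long one can still be found.

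**The case against.** Four points can be made for the plan.

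1. **The documents give no time course for distress.** A reader might infer from the schedule that an acute reaction would be over before it is measured, and that the trial would then report no harm. The protocol does not support that. It says nothing about duration, and the last row of the table shows that a large, slow reaction would probably be detected. The supportable word is could.
2. **A randomised comparison does reach into the early months.** A reader might infer that nothing randomised sees the first 22 weeks. The interim comparison of incident depression and suicidal behaviours contradicts that, and mental health service use is also collected at follow-up. This narrows the gap to distress below the level of an episode and to absenteeism, and does not close it.
3. **The harm sentence is a stated expectation and names 6 and 12 months.** That is correct, and it would be unfair to call the sentence wholly unqualified. The gloss that follows, however, drops the time points and becomes general.
4. **The schedule has a reason and the early period was considered.** The 6- to 12-month follow-up rests on reviews of risk-communication trials, and health status can be read to include mental health. The 1-month interviews address emotional effects and are used to triangulate the quantitative results. Measuring persistent distress is a legitimate design choice. It does not license a conclusion about distress in general.

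**Conclusion.** The point holds as a limit on what may be concluded, not as a flaw that invalidates the trial. The comparison remains sound for distress and absenteeism present at 6 and 12 months. It cannot support the general statement of no psychological or functioning harm, because no randomised comparison of those outcomes covers about the first 22 weeks.

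That figure needs only the protocol's schedule and recall periods. The size of what could be missed is conditional: with an initial 0.50 SD and a half-life of 4 to 8 weeks, 0.01 to 0.06 SD remains at week 24, and 6-month power is about 3% to 7%. With a half-life of 26 weeks it is 57%. The change matters because it alters what the trial may say on its second research question.

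**What to change.** In Statistical analysis, and in the reported conclusion, limit the harm statement to distress and absenteeism present at the 6- and 12-month interviews. Add one sentence saying that short-term distress after disclosure is not tested by a randomised comparison. Present the 1-month interviews as descriptive evidence from the intervention arm, and the interim event comparison as bearing on severe reactions only.

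A retrospective question about the worst weeks since the baseline call is not an adequate substitute. Under Blinding and follow-up assessments the protocol accepts that participants may know their group, and only the intervention arm was told its risk at that call, so recall error may differ by arm. It is best left out. If it is asked, it should be reported as exploratory with that caveat.

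The cost is wording and a narrower safety claim. No new data are needed, so the change remains possible although recruitment is complete.
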